#### Study Covariates

Demographics (age, sex, race), premorbid conditions (migraines and other headaches, depression, ADD/ADHD, other learning disorders, and other psychiatric illnesses), prior mTBI history and duration of symptoms, baseline academic performance, provider type (e.g., APP/Physician) and specialty, initial number of mTBI symptoms, and mechanism of injury.

#### Subgroup Analyses

The following planned subgroup analyses will be conducted in order to assess for heterogeneity of treatment effects: (1) Patients seen by resident physicians will be compared with those not seen by a resident, (2) patients treated by providers in compliance with the protocol will be compared to those who were not, (3) patients who received school accommodations will be compared with those who did not, (4) the effectiveness of the interventions will be compared across provider type and specialty.

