**IMPLEMENTATION**		
**Numerator** # of individual *TEaM* intervention components implemented **Denominator** Total # of *TEaM* intervention components **Data sources** eMR informal interviews focus groups among providers site visits observations	**Definition** Degree of *TEaM* intervention components consistently implemented across sites **Setting/*****TEaM*** **intervention components** **ED and UC settings** 1. Provider Training Modules 2. eMR Triage screening/provider alert 3. eMR Concussion Smart Form Template (documentation, decision support, management pearls) 4. Triggered by eMR Concussion Smart Form Template → CDC evidence-based discharge instruction →Communication Linkage Letters - Return to School with suggested accommodations - Return to Primary Care with ED findings **Primary care settings** 1. Concussion Academy Skill Training (CAST) and Training Modules 2. eMR Concussion Smart Form Template (documentation, decision support, management pearls) 3. CDC ACE tool (45, 46) 4. CDC ACE care plan/education (45, 46) 5. Linkage letters - Return to School with STAMP suggested accommodations and supports	Understand variations of implementing the *TEaM* Intervention components Approach to adapting each component of the *TEaM* Intervention across delivery systems Implementation barriers and facilitators of the *TEaM* Intervention including contextual factors and operational practices and how they were addressed

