## Methods

### Study Design Overview

The *TEaM* study is a combined randomized and 2 × 2 quasi-experimental study design with training and technology interventions occurring at the provider level involving ED, UC, PC healthcare providers (HCPs) across the Children's Healthcare of Atlanta system, with patient and school outcomes as key endpoints. At the HCP level, this study is randomized, and at the patient level, this study is a quasi-experimental with a pre and post design to facilitate analysis of the impact of our Electronic Medical Record (eMR) support tool on children's health outcomes.

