### *TEaM* Intervention

The *TEaM* Intervention was developed by the investigators through rigorous evaluation of the literature, incorporation of the CDC guidelines (23, 45, 46), and assimilation of best practices currently adopted by national experts (31, 45). The *TEaM* Intervention will be adapted for this study in collaboration with stakeholders from pediatric neuropsychology, emergency medicine, neurosurgery, sports medicine, primary care, ambulatory care, clinical informatics, nursing, school linkage experts, educators, school health personnel, as well as members of the CDC Pediatric Mild Traumatic Brain Injury Guideline Workgroup (23). The intervention consists of provider training in mTBI evaluation, care coordination and management protocols, eMR decision support system, and linkage materials. The eMR will be leveraged to refine the provider training portion of the intervention to improve screening, management, and linkage throughout the clinical care continuum with the goal of producing an effective and scalable intervention aimed at reducing mTBI-related school problems/performance, improving patient symptom recovery, and reducing post-injury complications. The *TEaM* Intervention is designed to enhance adoption and standardize best practices; the study tools are designed to fully function without interfering with a system that already has a high-functioning mTBI program. Most importantly, this intervention enables potential generalizability across various clinical settings; thereby, improving the translation and adoption of evidence-based management for patients, caregivers, providers, and school personnel to promote recovery following pediatric mTBI.

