## Data Collection

### Reach (Provider Level): Is the *TEaM* Intervention Reaching HCPs Diagnosing and Managing Children With mTBI?

We will determine how many and what proportion of HCPs receive *TEaM* Intervention training within each proposed site (ED, UC, PC) (36). The numerator is defined as the number of HCPs who agree to participate and receive the *TEaM* Intervention training. The denominator is defined as the total number of potential HCPs who are eligible for the study across each study site (53). We will consider representativeness by identifying similarities and/or differences between HCPs (intervention vs. control group and participation vs. non-participation). Comparisons among the control and intervention groups regarding compliance to the protocol and basic demographic characteristics will also be assessed (36). Qualitative inquiry will complement our data collection on Reach. Our objective is to understand how HCPs perceive the *TEaM* Intervention training, including barriers and facilitators to recruitment, participation, and non-participation across sites (38). Data sources will include eMR, provider questionnaires, semi-structured interviews, focus groups, and attendance records from provider training.

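### Provider compliance and receipt of school accommodations are targets of the intervention, arising after randomisation, so they are not valid subgroups for treatment-effect heterogeneity

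*Protocol article*

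**What the plan says.** The Subgroup Analyses section gives one purpose for all four items: "planned subgroup analyses will be conducted in order to assess for heterogeneity of treatment effects". Item (2) reads "patients treated by providers in compliance with the protocol will be compared to those who were not" and item (3) reads "patients who received school accommodations will be compared with those who did not". Item (1) concerns resident involvement and item (4) provider type and specialty.

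Four other places show where compliance and accommodations sit in the causal order:

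- Study Design Overview: "At the HCP level, this study is randomized".
- *TEaM* Intervention: "The intervention consists of provider training in mTBI evaluation, care coordination and management protocols, eMR decision support system, and linkage materials".
- Table 1, Implementation: the components include a linkage letter, "Return to School with suggested accommodations", in the emergency and urgent care settings, and "Return to School with STAMP suggested accommodations and supports" in primary care.
- Reach: the evaluation includes "Comparisons among the control and intervention groups regarding compliance to the protocol".

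The primary outcome is the CLASS-3 Academic Problems scale at weeks 1, 2 and 4, analysed by intention to treat.

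**The concern.** A subgroup can show effect modification only if allocation does not influence who belongs to it. Provider training, decision support and accommodation letters are meant to raise compliance and the use of accommodations. The children who receive accommodations in the intervention arm are therefore not the same kind of children as those who receive them in the control arm, and the same holds for the children who do not. The balance that provider randomisation gives is lost inside each stratum.

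Accommodations also plausibly go to children with more school difficulty, which is close to what the primary outcome measures. A direct comparison of accommodated with non-accommodated children would then tend to make accommodations look harmful.

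At stake is a published subgroup statement in either direction: a benefit in both strata where none exists, or an apparent harm from one of the intervention's own mechanisms.

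**Working it through.** **Structural check.** The article states no figure on this point, so there is none to reproduce. The question is whether each variable could be changed by allocation.

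| Item | When determined | Changed by the intervention? |
|---|---|---|
| (1) resident involvement | at the visit | not a direct product of it |
| (2) provider compliance | after provider randomisation | yes: training, protocols and decision support aim at it, and Reach plans to compare it between arms |
| (3) school accommodations | after the index visit | yes: the linkage letters suggest them |
| (4) provider type and specialty | provider characteristic | no |

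**Illustration for item (3).** Every input is an assumption; none is in the article.

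- Severity S is standard normal. The outcome Y has SD 1, with higher values worse, and correlates 0.5 with S.
- Neither arm nor accommodations has any effect on Y.
- Receipt is 30% in control and 60% in intervention. There is no covariate adjustment.

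*Sharp cut-off* (the most severe children receive accommodations). If a proportion p receives them, mean S is φ/p among recipients and −φ/(1−p) among the rest, where φ is the normal density at the cut-off.

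- Control, p = 0.30, φ = 0.348: 1.159 and −0.497.
- Intervention, p = 0.60, φ = 0.386: 0.644 and −0.966.
- Arm difference among recipients: 0.5 × (0.644 − 1.159) = −0.26 SD.
- Arm difference among non-recipients: 0.5 × (−0.966 + 0.497) = −0.23 SD.

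*Probabilistic receipt* (probit in S with slope b). The sharp-cut-off values are multiplied by b/√(1+b²), which is 0.447 for b = 0.5 and 0.707 for b = 1.0. Simulation with 2,000,000 patients per scenario gave:

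| Receipt, control / intervention | b | Arm difference, received | Arm difference, not received | Received minus not received |
|---|---|---|---|---|
| 30% / 60% | 0.5 | −0.12 | −0.10 | +0.33 |
| 30% / 60% | 1.0 | −0.18 | −0.17 | +0.52 |
| 20% / 70% | 1.0 | −0.32 | −0.29 | +0.45 |
| 30% / 30% | 1.0 | 0.00 | 0.00 | +0.58 |

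The closed form agrees: for 30%/60% and b = 1.0, 0.707 × 0.5 × (−0.515) = −0.18 among recipients and 0.707 × 0.5 × (−0.469) = −0.17 among the rest. The overall arm difference was zero to within 0.001 in every scenario.

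The within-stratum arm bias needs receipt to differ between arms, which is what the intervention aims for. The comparison of received with not received needs no such difference: it stays at +0.58 SD with equal receipt, through severity alone.

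**Item (2).** The structural argument is the same, but no size was computed. It would need compliance rates by arm and the strength of the causes that compliance shares with the outcome, and the article gives neither.

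**The case against.** Five points can be made for the plan.

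*The list is compressed wording in a condensed article.* The lead sentence names heterogeneity and item (4) speaks of effectiveness, so items (1) to (3) may be meant as comparisons of the intervention effect across levels. That is a fair reading, and interaction terms and interval estimates are normally left to an analysis plan. It settles items (1) and (4). It does not rescue (2) and (3), because the difficulty lies in the variables the article has chosen.

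*The within-stratum and between-level figures describe different analyses.* They do, and they are alternatives. Only one can apply, depending on what the section means. Neither serves the stated purpose.

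*Covariates could deal with the selection.* Study Covariates lists the initial number of symptoms, baseline academic performance and premorbid conditions. In the illustration severity is the only confounder, so full adjustment for it would remove the bias. In practice, adjustment could reduce the bias but cannot be assumed to remove it, and the article does not tie these covariates to the subgroups.

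*The illustration is strong.* The sharp cut-off is an extreme case: its values are about 1.4 to 2.3 times those from probabilistic receipt at the same rates.

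*A reader might infer that the bias equals the effect the trial is sized for.* The documents do not support this. A standardised difference of 0.27 follows only from a back-calculation for a simple two-group comparison of 425 analysed patients at 80% power: (1.960 + 0.842) × √(2/212.5) = 0.27. The Sample Size section itself prints a Cohen's value of about 0.15. Neither is a sound yardstick for a bias whose inputs are all assumed.

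**Conclusion.** The point stands. Items (2) and (3) are fixed in the article as heterogeneity subgroups, and both are determined after provider randomisation and are targets of the intervention. Arm contrasts within them are open to selection bias. Contrasts between their levels are confounded by indication and contain no arm comparison.

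Under the stated assumptions (no true effect, correlation 0.5, 30% against 60% receipt, no adjustment), the spurious within-stratum benefit is about 0.10 to 0.18 SD with probabilistic receipt and up to about 0.26 SD with a sharp cut-off. With probabilistic receipt, received against not received differs by about 0.3 to 0.6 SD across the scenarios. These figures show that the bias can matter; they do not estimate it for this trial.

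A reader might go further and infer that the trial's main conclusion is compromised. It is not: the primary analysis is by intention to treat, with its own α level, and does not use these subgroups. Nor are items (1) and (4) at fault. This is a defect of supplementary analyses that should be corrected before results are seen.

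**What to change.** 1. Take items (2) and (3) out of the treatment-effect heterogeneity list.
2. Report school accommodations and provider compliance as outcomes by arm.
3. Label any comparison by accommodation or compliance status as descriptive and non-causal. Alternatively, replace it with an exploratory mediation or complier-type analysis, but only if compliance is defined in both arms (the article does not say what it means for a control provider) and the assumptions are stated. For a complier-type analysis with allocation as instrument, these include the exclusion restriction. That is doubtful here, because training, decision support and linkage materials can each act on outcome by other routes, and the Study Design Overview assesses the eMR tool by a pre/post comparison at patient level.
4. Keep items (1) and (4) as heterogeneity analyses, read as comparisons of the intervention effect across subgroup levels.

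The cost is a change of wording, modest extra analysis and two fewer subgroup claims. No new data are needed.

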### Participants/Setting

Participants in this study include HCPs in ED, UC, and PC settings affiliated with Children's Healthcare of Atlanta. HCPs will include Physicians and Advanced Practice Providers (nurse practitioners and physician assistants). HCP level randomization will be stratified by practice site to ensure that the distribution of control and intervention providers is approximately equal within sites. Providers will be sent an electronic informed consent form (eICF) using Research Electronic Data Capture (REDCap™) tools (52) for consent to participate.

Children ages 5–18 years old who screen positive and/or are diagnosed with mTBI/concussion will be recruited following discharge from their index injury visit, which may have occurred in either ED, UC or PC settings. Regular reports of children who screen positive through the decision support tool will be sent to the research team throughout the 32-month study period. After confirmation of an evaluation by a participating provider and either a positive screen or diagnosis of mTBI/concussion, an initial phone call will be made to the parent.

Upon the first contact, the parent will be given a very brief explanation of the study at which point, an option to opt-out will be offered. If they choose to opt-in, a simple validated symptom questionnaire, the CDC Acute Concussion Evaluation (ACE) tool (45) will be used to ensure that the child meets eligibility requirements. At this point, if the child is eligible, parental verbal consent will be obtained in order to proceed with further explanation of the study. A total of 532 consecutive children (see section Data Analyses) with mTBI meeting inclusion/exclusion criteria will be recruited. The goal is to maintain a lost to follow up (LTF) rate of <20% for a total sample of 425. Enrolled children will be treated for up to 6 months post-injury to assess the impact of the *TEaM* Intervention on pediatric mTBI-related outcomes.

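### Two planned heterogeneity subgroups (provider compliance and receipt of school accommodations) are observed after provider randomisation and can be affected by arm, so they cannot show treatment-effect modification

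*Protocol article*

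**What the plan says.** The Subgroup Analyses section opens with its purpose: "The following planned subgroup analyses will be conducted in order to assess for heterogeneity of treatment effects". Four items follow. Item (2) reads "patients treated by providers in compliance with the protocol will be compared to those who were not" and item (3) reads "patients who received school accommodations will be compared with those who did not". Neither is labelled exploratory or non-randomised, and neither is given a causal method or an adjustment set of its own.

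Four other places bear on when these factors arise:

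- **Study Design Overview:** "At the HCP level, this study is randomized, and at the patient level, this study is a quasi-experimental with a pre and post design".
- **Participants/Setting:** children "will be recruited following discharge from their index injury visit", after a participating provider has seen them.
- **Table 1, Implementation row:** the intervention components include linkage letters, described for emergency and urgent care as "Return to School with suggested accommodations" and for primary care as "Return to School with STAMP suggested accommodations and supports".
- **Reach section:** "Comparisons among the control and intervention groups regarding compliance to the protocol and basic demographic characteristics will also be assessed".

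**The concern.** A subgroup can test whether a treatment effect varies only if membership could not have been altered by the treatment. Age or provider type meets that condition. Compliance and accommodations do not: each comes after allocation, and the intervention is designed to influence each.

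Two problems follow. First, items (2) and (3) as worded compare children with and without the factor. That is an observational contrast, open to confounding by how badly the child was affected. Second, rewriting them as intervention versus control within each stratum does not restore a randomised comparison. If the arm changes who enters a stratum, the two arms within it contain different mixes of children.

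The primary endpoint is academic problems at school, and accommodations are the component closest to it. A misleading subgroup result there could be read as advice on return to school.

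**Working it through.** **Step 1: timing and dependence on arm.**

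| Factor | When it is known | Can the arm change it? |
|---|---|---|
| (2) Provider compliance | After allocation, from provider behaviour | Yes: training and tools differ by arm, and the Reach section plans to compare compliance between arms |
| (3) School accommodations | After allocation, visit and return to school | Yes: the letters in Table 1 suggest them |
| (4) Provider type and specialty | Before allocation | No |

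Item (4) is sound in this respect. Items (2) and (3) are not. This step uses only the article's text.

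**Step 2: illustration for accommodations.** The article gives no uptake rates and no link between severity and accommodations, so every input here is an assumption.

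- Severity S is standard normal; arms are 1:1.
- P(accommodation) = expit(a + 0.9·S), with a = −0.95 in control and 0.45 in intervention.
- Outcome Y = ρ·S + noise, SD 1, higher is worse, ρ = 0.3, 0.4 or 0.5. Neither arm nor accommodation has any effect.

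Integrating over S gives uptake of 0.307 (control) and 0.595 (intervention), and these mean severities:

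| | Control | Intervention | Both arms |
|---|---|---|---|
| Accommodated | 0.5395 | 0.3117 | 0.389 |
| Not accommodated | −0.2392 | −0.4575 | −0.320 |

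Because Y depends only on S, each contrast is ρ times a difference in mean severity:

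- Accommodated minus not: ρ × (0.389 + 0.320) = ρ × 0.709 = **+0.21, +0.28, +0.35 SD**.
- Arm difference among accommodated: ρ × (0.3117 − 0.5395) = ρ × (−0.2278) = **−0.07, −0.09, −0.11 SD**.
- Arm difference among not accommodated: ρ × (−0.4575 + 0.2392) = ρ × (−0.2183) = **−0.07, −0.09, −0.11 SD**.
- Arm-by-stratum interaction: ρ × (−0.0095), about 0.
- Intention-to-treat difference: 0.

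If accommodations themselves helped by 0.30 SD, the first contrast would shift by −0.30. At ρ = 0.5 it becomes 0.35 − 0.30 = +0.05, the wrong sign. At ρ = 0.3 it becomes 0.21 − 0.30 = −0.09, the right sign but less than a third of the true size.

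**Step 3: what adjustment does.** Adjusting for a baseline proxy that correlates r with severity leaves the fraction (1 − r²)/(1 − r²k²) of the crude contrast, where k is the correlation of accommodation with severity. Here k = 0.709 × √(0.451 × 0.549) = 0.353. With r = 0.6 the fraction is 0.64/0.955 = 0.67, so +0.14 to +0.24 SD remains. A perfect measure of severity (r = 1) would leave nothing in this model.

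**Step 4: illustration for compliance, also assumed.** Let P(compliance) = expit(0.5 + S) in intervention (60%) and expit(−1) = 27% in control regardless of severity, with ρ = 0.5 and no true effect. Mean severity is 0.33 in intervention compliers, −0.50 in intervention non-compliers and 0 in both control groups. The arm difference is then 0.5 × 0.33 = +0.17 SD in compliers and 0.5 × (−0.50) = −0.25 SD in non-compliers. If severity drives compliance equally in both arms, the differences are −0.13 and −0.12 SD: biased, but with almost no interaction.

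**The case against.** The best defence is that these are secondary analyses, that Study Covariates lists initial number of mTBI symptoms and baseline academic performance, and that the choice of covariates for each model belongs in an analysis plan that is not shown. Much of this stands. The intention-to-treat primary analysis is untouched, and adjustment could shrink the bias. But the article does not tie those covariates to the subgroup items, Step 3 shows that an imperfect proxy leaves much of the bias, and no adjustment turns a factor affected by the arm into a baseline modifier. An analysis plan can add detail; here the article has already fixed the purpose of these two items.

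The severity link is also an assumption. Table 1 says that in emergency and urgent care the school letter is triggered by the electronic form, which could weaken the dependence on severity in the intervention arm.

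A reader might infer four stronger points, which the document does not support:

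- **The intervention creates these subgroups.** Nothing suggests that control children cannot receive accommodations. The factors can be affected by arm, which is enough.
- **Compliance has no meaning for control providers.** The Reach section plans to compare it in both arms.
- **False heterogeneity is to be expected.** In the accommodation illustration the interaction is about 0. It appears in Step 4 only when severity acts on compliance in one arm.
- **The bias can be measured against the planning effect of about 0.15.** That is an arm effect. A 0.15 SD benefit of accommodations themselves would imply an intention-to-treat difference of only 0.15 × (0.595 − 0.307) = 0.04 SD.

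**Conclusion.** The point holds as a should-fix. That items (2) and (3) are post-randomisation, can be affected by arm and are wrongly listed as tests of effect modification follows from the article's own text and needs no numerical assumption.

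The size and direction of bias do rest on assumptions. Under those of Step 2, accommodated children look 0.21 to 0.35 SD worse with no true effect, and a spurious benefit of 0.07 to 0.11 SD appears in both strata. A wrong sign is possible, not certain. A reader might infer that the trial's main conclusion is at risk. It is not: the primary comparison does not use these subgroups.

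**What to change.** 1. Remove items (2) and (3) from the heterogeneity list.
2. Report receipt of accommodations and provider compliance by randomised arm, as intermediate and implementation outcomes.
3. Keep any received-versus-not or complier-versus-non-complier comparison only as an exploratory, non-randomised analysis adjusted for pre-visit severity (for example initial number of mTBI symptoms and baseline academic performance), or as a mediation analysis with its assumptions stated.
4. A complier-average analysis is optional. It needs a definition of compliance that applies in both arms and a stated exclusion restriction, which is doubtful for a package with several components.
5. Limit heterogeneity tests to factors fixed before allocation or before the visit, such as item (4), and test them as arm-by-factor interactions.

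The cost is rewording one section and a little extra analysis. No new data are needed, and sample size and primary analysis stay as they are.
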